### Randomization

Before completing the baseline assessments, participants will be randomly allocated to the intervention or control group. The research team will assign the patient to the groups using randomization schedules generated by UCLA Biomathematics for group assignment in blocks of 4. As each patient is enrolled, he or she will be assigned to the next number on the list and the associated condition, yoga or usual care.

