**Figure 3 F3:**
[figure not shown]
**Selected yoga poses**.

Yoga taught in the Iyengar tradition is known for an extensive teacher training program. Iyengar teachers study for at least seven years before being certified to work with students who have therapeutic needs. They must pass several certification tests before an impartial national board. These tests include teaching, performance of poses and breathing techniques, anatomy and therapeutic sequences. Because of this training, IY teachers across the country and around the world can accurately reproduce the IYP in this study.

The proposed IYP will be administered twice a week for 1.5 hours duration per session for 6 weeks. Due to the extensive time commitment required for the IYP, there will be no instructions for home practice, but neither will participants be discouraged from practicing at home. At the end of the 6-week IYP, those participants who ask for referrals to IY studios/teachers in the community will be given a list of referrals. All home practice as well as post-IYP yoga classes will be monitored during the weekly phone calls/e-mails and at the post-treatment and follow-up assessments; the extent of home practice will be evaluated in the analyses for its potential impact on outcome.

Should subjects experience a flare-up during the IYP, the research team will consult with the patient's rheumatologist and a modified version of the IYP will be offered to the subject consisting of restorative poses that do not place strain on the affected joints.

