**9. *Medication use ***will be assessed during the patients' weekly phone call/e-mail during which the ***Weekly Monitoring Form ***will be administered. These weekly forms will be used to gather ratings of patients' pain, fatigue, anxiety and depression using 0-10 scales; we will also assess the extent of physical activity during the past week and the extent (i.e., frequency/duration) of any home practice of yoga.

A ***weekly monitoring form ***will include specific questions about functioning, mood, pain, improvement, activity and medication use. The form is an important tool as patients' self-reported functioning will form the basis for understanding the action of yoga over time on symptoms. Thus, responses to the form will be used to determine the minimum and maximum number of yoga sessions needed to produce change. For participants who prefer completing this form online, an online link will be sent to them each week. Otherwise, the form will be telephone-administered by a trained research assistant once a week for two weeks preceding the intervention to ascertain baseline functioning, and then once a week during the intervention and control periods.

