### Exploratory analyses for potential mediators and moderators

We will also examine potential mediators and moderators of treatment outcome. Regression analyses will be conducted to determine whether sociodemographic or clinical characteristics mediate or moderate treatment outcome. We will follow the procedures outlined in Cohen and Cohen [75] to calculate residualized change scores for the SF-36, PDI and the HAQ. Multiple regression analysis will then be conducted with outcomes separately; change scores (baseline minus post-treatment) will be regressed onto a set of predictor variables including group (yoga vs. control), the mechanism of interest (e.g., self-efficacy) and the interaction between the mediator/moderator and group. A significant interaction term indicates moderation [76] and post-hoc analyses will be conducted to examine the moderator variables. If evidence of mediation is found using the traditional Baron and Kenny approach, the Sobel test, a statistical test for mediation will be conducted to yield a more precise picture of mediation. Exploratory analyses will be conducted in the data derived from the weekly monitoring forms; for example, we will examine whether changes in overall physical activity may moderate treatment outcome.

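### Change in physical activity during treatment is planned as a moderator of yoga, but it is measured after randomisation and yoga can alter it, so a significant interaction is not evidence of effect modification (minor)

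*Protocol article*

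**What the plan says.** The section on exploratory mediators and moderators describes a regression of outcome change on group, the variable of interest and their interaction, and gives the reading rule: "A significant interaction term indicates moderation". It then adds that "Exploratory analyses will be conducted in the data derived from the weekly monitoring forms" and offers one example: "we will examine whether changes in overall physical activity may moderate treatment outcome".

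Under Exploratory variables (item 9, the weekly monitoring form), the activity item is summarised as follows: "we will also assess the extent of physical activity during the past week and the extent (i.e., frequency/duration) of any home practice of yoga". The telephone version of the form is given "once a week for two weeks preceding the intervention to ascertain baseline functioning, and then once a week during the intervention and control periods". The Design section has both arms contacted weekly.

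On timing, the Randomization section says: "Before completing the baseline assessments, participants will be randomly allocated to the intervention or control group". On dose, the Intervention section says: "The proposed IYP will be administered twice a week for 1.5 hours duration per session for 6 weeks".

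**The concern.** A variable supports a statement about effect modification (yoga works better in people with more of X) only if treatment does not influence X. In practice that means a baseline characteristic. Activity change over the treatment weeks is not one. Hypotheses 2 and 3 expect yoga to improve functioning, pain, disease activity and mood, and people who feel and function better may well do more. Activity change may then be a consequence of response to yoga rather than a condition for it.

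If so, an association between activity change and outcome change that is present in the yoga arm and weaker in the control arm will appear as an interaction. The stated rule would label it moderation. The group coefficient in the same model is also conditioned on something that lies downstream of group.

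What is at stake is the use made of the result. The Discussion presents these analyses as a first step towards identifying moderators and mediators, and the study is meant to inform a larger trial. A spurious moderator could be carried into that design.

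**Working it through.** **Timing.** Randomisation precedes the baseline assessments. The weekly form runs for two weeks before the intervention and then through the intervention or control period. The protocol does not define the change score, but any change from the pre-intervention forms to the treatment-period forms is completed after allocation and during treatment.

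**Routes from yoga to activity.** (a) Improvement leads to more activity; this holds whatever the item counts. (b) Class hours are counted as activity: 2 sessions × 1.5 h = 3 h/week, or 12 × 1.5 h = 18 h over six weeks, with none in the control arm. Route (b) is conditional, because no section says whether class time is inside or outside the item.

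**Illustration of size.** From the document: about 28 completers per arm. Assumed, not in the documents: the item is in hours; the SD of change in non-class activity is s = 2, 3 or 5 h/week; yoga improves the outcome by 0.5 SD; and for route (a), each SD of improvement in the yoga arm adds k = 0.8 h/week. There is no true moderation. The model is outcome change on group, activity change and their product, with 5,000 simulated trials per setting.

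*Route (b) alone, s = 2, every class attended.* The interaction test rejects in 4.9% of trials with classes excluded and 5.6% with classes counted. With variable attendance and classes counted it rejects in 5.4%. All are close to the nominal 5%. With full attendance, the cost is precision: the SD of the group coefficient rises from 0.27 to 0.40.

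*Route (a), classes excluded.* In the yoga arm, the slope of outcome on activity change is k/(s² + k²); in the control arm it is 0. For s = 2:

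- Slope difference: 0.8/(4 + 0.64) = 0.172.
- Yoga-arm residual variance: 1 − 0.64/4.64 = 0.862.
- Standard error: √[0.862/(27 × 4.64) + 1/(27 × 4)] = √(0.00688 + 0.00926) = 0.127.
- Ratio: 0.172/0.127 = 1.36.
- Rejection: P(Z > 1.96 − 1.36) ≈ 0.27.

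| s (h/week) | slope difference | ratio to SE | rejection, formula | rejection, simulation |
|---|---|---|---|---|
| 2 | 0.172 | 1.36 | 27% | 27% |
| 3 | 0.083 | 0.95 | 16% | 15% |
| 5 | 0.031 | 0.58 | 9% | 8% |

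With k = 0, simulated rejection lies between 4.5% and 5.2% across the three values of s.

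*Routes (a) and (b) together, s = 2.* Rejection is 26%, so counting classes adds nothing to the false interaction. The group coefficient, however, falls from 0.50 to about 0. In a model with an interaction it is the arm difference at zero activity change, and the yoga arm now sits 3 h/week above zero: 0.50 − 3 × 0.172 = −0.02. For s = 3 and 5 the same step gives 0.25 and 0.41.

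**Overlap with group if classes are counted.** The standardised arm difference is d = 3/s and its correlation with group is d/√(d² + 4): 0.60, 0.45 and 0.29 for s = 2, 3 and 5. These values need classes counted, an hours scale and the assumed SD.

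**The case against.** The strongest objection is to a reading that goes further. A reader might infer that the weekly form counts the yoga classes, so that the moderator is partly the treatment itself and a significant interaction would merely reflect class attendance. The document does not support this. The form is only summarised, home practice is recorded alongside activity, class hours are not mentioned, and assistants record attendance separately (Phase two). Exact item wording is something a journal article commonly leaves out. The word overall, and the description of yoga as a form of physical activity in the section on yoga as an innovative approach, make inclusion plausible but no more. Nor does the attendance mechanism work as supposed: counting classes alone left the interaction test near 5%.

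Three further objections have some force. The activity sentence names no model, so applying the regression described just above it is an inference, although a natural one given the word moderate. The same section offers a mediation route. And this is a single example under an exploratory heading, in a study that says it does not propose to test every pathway; the treatment effect is judged from the group-by-time analysis, not from this regression.

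All of this narrows the point and lowers its weight. It does not remove the core: a change measured during treatment, which treatment can affect, is named as a moderator.

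**Conclusion.** The point holds, as a minor one. Because activity change is measured after allocation and yoga can affect it, a significant interaction cannot be read as effect modification, and the group coefficient in that model may be adjusted for part of the treatment effect. This conclusion rests on the timing stated in the protocol and on the plausibility of yoga affecting activity. It does not require class hours to be counted; if they are, the effect is mainly on the precision and meaning of the group coefficient.

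The illustrative size is a false-interaction rate of about 8% to 27% against a nominal 5%. It depends on the assumed strength of the path from improvement to activity and on the assumed SD, and it returns to about 5% if yoga has no such effect. No primary or secondary conclusion is touched.

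**What to change.** In the exploratory analysis section, name activity from the two pre-intervention weekly forms as the moderator. Because randomisation comes before the baseline assessments, these forms may also be completed after allocation; where possible, have them completed before allocation is disclosed.

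Report change in activity outside study classes by arm, as an outcome or candidate mediator and not as a moderator. State that study classes are excluded from the activity item. That wording clarifies the variable, but on its own it would not cure the interaction test, since the inflation above arises with classes excluded.

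The cost is about one sentence in the analysis section, a clarification of one form item if it does not already exclude classes, and attention to when the first forms are sent. The pre-intervention forms are already planned. The downside is that activity change is no longer tested as a moderator.

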### Qualitative analyses

Digitally recorded qualitative data will be transcribed and entered into computer files. Data in these forms consist of large verbal texts that must be interpreted, organized, and summarized using a text-based analysis technique. The technique most appropriate to our data and research goals is ethnographic content analysis (referred to as template text analysis by Crabtree and Miller, 1992) because we wish to systematically integrate it with the close-ended HRQOL and functionality data. This technique involves the creation of a codebook based on variables identified by the researcher as relevant to the research questions and goals. Texts are read and codes are assigned to relevant portions of the text and entered. The process is iterative, however, and code categories are revised, expanded, and created as research progresses. This requires that coding proceeds from the very beginning of the research and updating of previously coded materials is carried out as the coding is refined.

We will employ Dedoose, one of the most effective qualitative data analysis tools currently available. Employing a web-based interface, Dedoose was designed primarily for team-based research projects and includes features that allow for efficient coding, integration with categorical and scale data, and database searching and retrieving. Unique to Dedoose is the ability for research team members with security clearances from the PI to access the data. All transfer of project data is encrypted for security. Further, the process of identifying and exploring coding patterns is automated via easily generated tables and user-defined output is available at any time in MS Word or Excel formats.

The process of coding allows for the thematic analysis of data. To address inter-rater reliability concerns, we will use multiple coders and measure intercoder agreement (the extent to which a group of individual coders concur in their identification of themes and codes). Thus, we will be able to ensure a high level of reliability in our qualitative data analysis.

### Integrating methodologies

For this study, the qualitative interviews derive a number of themes from the HAQ and the PDI. Our intention in doing so is to delve into how pain limits the HRQOL of young people with RA in much greater depth than the quantitative measures alone allow and to triangulate the findings. The qualitative instrument seeks to capture in detail the nuances of the impact of RA on the respondents' life experiences in seven domains: 1) family/home responsibilities, 2) recreation (hobbies, sports), 3) social activity, 4) occupation, 5) sexual behavior, 6) self-care, and 7) life-support activity (eating, sleeping, breathing). We will explore in detail the nature of the subjects' symptoms and what life domains the symptoms affect, how specifically these life domains are impacted, the patients' attempts at self-management of the symptoms, impact of the symptoms on these networks, and the patients' perceptions of the effects of the yoga program.

The integration of qualitative and quantitative methodologies represents a promising, though largely underutilized, avenue for researchers. An emergent and compelling body of literature supports the value of mixed methods [77-80] and suggests a panoply of means by which the techniques can be effectively combined. In this study, we are electing to administer quantitative measures as well as a qualitative measure that derives its basis from the quantitative measure in order to: a. cross-validate the qualitative and quantitative data (triangulation), b. clarify the data from one method with the data of another (complementarity), and c. broaden the depth of the data (expansion) [79]. Overall, we intend to optimize our understanding of the effects of the IYP for this population; we believe this integrated methodological approach will yield a much richer set of data than if we were to follow either strategy alone and distinguishes our proposed study as unique.

## Protection of subjects

This study was approved by the South General Institutional Review Board within the Office of the Human Research Protection Program at UCLA (IRB Number G08-02-045-03). The study will be carried out in compliance with the Helsinki Declaration.

### Potential risks

Yoga is generally regarded as safe and adverse effects are rare, especially within the Iyengar program in which props are used for support and teachers undergo vigorous training. A number of case reports have indicated adverse events following yoga, specifically, the presence of subcutaneous emphysema [81] and shortness of breath and chest pain [82]. However, these events were in response to intensive *pranayama*, or breathing exercises, with the shortness of breath case experiencing difficulty following *kapalabhati pranayama*, involving strong forced breaths which may push the body to physiologic extremes [82]. Such intensive breathing techniques will *not *be used in this yoga intervention. Back bending postures, such as those used in IY can be harmful if conducted without progressive musculoskeletal actions [83], and great care will be taken in developing the yoga program to ensure that muscles are not stressed. A qualified assistant in addition to the instructing teacher will also be present during all sessions to ensure that patients are completing the poses correctly. Participants may feel uncomfortable disclosing personal information about their mood and symptoms on study questionnaires and during interviews. The 28 joint count medical exam and blood draws may cause some temporary discomfort at the time of examination.

### Protection against risks

The major potential risks from the yoga class are musculoskeletal strains or injuries. We will minimize these risks by conducting the yoga intervention in the safest manner possible. A progressive series of poses has been developed for this trial; this gradual progression tailored to the participants is designed to avoid musculoskeletal injury. In addition, props will be used to support participants in more challenging poses. The general safety parameters of the yoga program are: 1) heart rate will not exceed moderate training range (115 BPM) - we will ask participants to check their pulse at the end of each yoga session during a timed one-minute period and to report their heart rate; 2) attention will be paid to spinal safety; 3) balance will be carefully monitored (e.g., chairs are used to assist balance as needed). Students will be given modifications of postures using props to accommodate for individual differences and limitations, and receive individual attention if postures are too challenging. An assistant will work with the experienced IY teachers during all classes and will observe for any difficulties and assist participants as needed.

To minimize any potential risks or discomfort associated with study assessments, all assessments will be conducted in a private room. Participants will be encouraged to raise questions or concerns at any time and be reminded that they may withdraw at any time without penalty. A trained phlebotomist will collect all blood samples and a rheumatologist will conduct the medical exams.

Confidentiality will be maintained by the use of unique identification numbers. All data and participant lists will be kept in locked file cabinets with access restricted to research staff. All data forms will have subject ID only. No data on individuals will be published. All hard copies of the data will be kept in locked file cabinets, even after the completion of the study. Data obtained from participants will be stored in a computer database, which will be password accessible only. Password-protected access will be given only to the principal investigator and co-investigators on the study. Electronic data will be collected using a secure survey software and questionnaire tool called SurveyMonkey with many system safeguards such as password protection, IP-masking, and data encryption (Secure Sockets Layer or SSL), etc. The hypertext transfer protocol secure (HTTPS) URL provides encryption and secure identification of the server, as indicated by a lock icon, to ensure confidentiality. SurveyMonkey is one of the most common secure online questionnaire services used to survey research participants and has physical and environmental controls in place to protect data.

### Yoga safety and adherence monitoring board

The Project Director will oversee the process of data collection and ensure that data from the medical evaluation, self-report questionnaires, and interviews are reviewed for completeness and accuracy. Reviewed data will be secured in locked file cabinets in the project offices. During each of the treatment waves, we will carefully monitor any potential threats to the safety and well-being of participants. A board will be created with the purpose of monitoring instructor adherence to the study manual and safety of patients. The Board will review the notes taken by assistants at each session for a randomly selected sample of 20% of patients, to be equally distributed across those who receive the IYP first and those who receive the control condition first. Using these notes, the Board will rate each instructor on the extent of adherence to the yoga manual. The Board will also review regular safety reports that will include information regarding recruitment, demographics of subjects, and any possible safety concerns including adverse events.

## Discussion

Young people with chronic, disabling RA symptoms represent a significantly underserved population. The overarching goal of this project is to develop and test a novel prevention and risk reduction approach to improving functioning and enhancing the quality of life for this population. The data from this project will inform a larger study to conduct a more formalized and advanced trial to further evaluate the utility of IY for improving pain and functionality among RA patients. Ultimately, by amassing a strong evidence base, our IY treatment protocol may eventually become integrated into the established prevention and treatment approach for RA as well as the management of other chronic and debilitating conditions.

A number of limitations may pose challenges to carrying out the proposed study. Given that RA is more typically diagnosed in older adults, recruiting participants who meet our age criteria may prove difficult. It is possible that attrition rates will be higher than predicted. A significantly greater drop-out rate would contradict our hypothesis about feasibility and this finding would force us to reconsider our design. Another potential study limitation is possible difficulties in scheduling the IYP sessions to avoid conflict with school or work and childcare issues. Classes will be scheduled on weekends and evenings at times when the majority of participants are available to address this potential difficulty. Participants will also have the opportunity to attend one make-up session if they miss any regular group classes. Another potential limitation will be the development of an arthritic flare during the IYP or control period. If a participant develops a flare, he or she will be instructed to communicate with his or her treating rheumatologist. The principal investigator will set up a meeting with the Data and Safety Monitoring Committee, which includes a rheumatologist. The Committee will develop a modified treatment plan so that the participant can remain in the IYP and continue with the program using modified poses.

We recognize that the control group does not account for the group or social aspects of the IYP. However, we will assess the extent of the social support using qualitative methods to determine the extent to which these aspects may impact outcomes. The decision to include a wait-list control group was based on the consideration that including a group-based control intervention would be premature at this early stage of the clinical trial process. We plan to explore the initial feasibility, safety and efficacy of the IYP before moving on to a large-scale clinical trial employing a group-based control condition that controls for group effects related to the IYP. It is also possible that the results of the study will reveal null findings and no significant differences will emerge between the control and intervention groups. If this is the case, analyses will be conducted to determine possible causes of negative findings. Perhaps the intervention will only be effective for a sub-group (such as young adults) or for a limited number of outcomes. These findings will, in turn, inform future investigations of yoga for RA. Even if null findings occur, post-hoc analyses will prove valuable in refining further work in this area.

Despite these limitations, our study is an innovative contribution to the field of yoga research. One of the more novel aspects of the study is that we will use a mixed methodology assessment. This approach will allow us to learn more from the participants in ways that will help ensure the success of future studies and may lead to the formulation of additional hypotheses. A key feature of this project is the building of this study within a theoretical model that will guide us in testing specific pathways for IY effects, including the impact of psychospiritual aspects of IY on functional and HRQOL outcomes. These analyses represent the first step in the eventual delineation of salient moderators and mediators of the effects of yoga in this population. Based on the present findings, the model can be more fully explicated and tested in multi-center studies with larger samples.

